## Abstract

**Background:**

Primary headache disorders, including migraine and tension-type headache, are among the most prevalent neurological conditions worldwide, significantly contributing to disability and socioeconomic burden. While Western medicine (WM) predominantly focuses on pharmacological symptom management, Korean medicine (KM) emphasizes a holistic, individualized approach using modalities such as acupuncture and herbal medicine. Collaborative treatment, which combines these approaches, has been proposed as an alternative approach; however, robust evidence on its clinical effectiveness and cost-effectiveness remains limited.

**Objective:**

This study aims to evaluate the clinical effectiveness and economic value of collaborative treatment compared with usual care (UC) in patients with primary headache disorders in real-world clinical settings.

**Methods:**

This prospective, 2-arm, multicenter observational study will assess and compare the clinical effectiveness and economic value of collaborative treatment versus UC alone for patients with primary headache disorders. Adults aged ≥19 years with a primary diagnosis of primary headache disorders visiting participating hospitals under South Korea’s national collaborative treatment pilot project will be enrolled. Participants will receive either collaborative treatment (integrating WM pharmacotherapy with KM therapies such as acupuncture, pharmacopuncture, and herbal medicine) or UC (monodisciplinary care with WM or KM alone) based on informed choice. Clinical and cost-related outcomes will be assessed at baseline and 6 and 12 weeks. Clinical outcomes include monthly headache days, the numeric rating scale, the Headache Impact Test, the EQ-5D-5L, and the EuroQol visual analogue scale. The cost-effectiveness evaluation includes the cost per quality-adjusted life year, the incremental cost-effectiveness ratio, and the cost-effectiveness acceptability curve. Both intention-to-treat and per-protocol analyses will be performed.

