## Methods

### Study Design

This is a prospective, 2-arm, multicenter observational study of patients with primary headache disorders at medical institutions participating in the fifth phase of the national pilot project for collaborative treatment [28]. The study protocol was developed following the SPIRIT (Standard Protocol Items: Recommendations for Interventional Trials) guidelines (Multimedia Appendix 1) and registered with the Clinical Research Information Service of South Korea (registration KCT0010812; July 28, 2025) [32]. The study will be conducted as part of the Registry for Korean Medicine and Western Medicine Collaborative Treatment study, with participant recruitment scheduled from the date of institutional review board approval to December 12, 2025. The detailed study schedule, as outlined in the SPIRIT guidelines, is illustrated in Table 1. Additionally, a schematic diagram displaying the study flow and timing of assessments is presented in Figure 1.

**Table 1 table1:** Schedule of enrollment and assessments according to the SPIRIT (Standard Protocol Items: Recommendations for Interventional Trials) guidelines.

			Study stage						
			Enrollment		Baseline and allocation		Treatment and follow-up		
							6 weeks		12 weeks

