**Assessments**									
	MHDs^a^			✓		✓		✓	
	NRS^b^			✓		✓		✓	
	HIT-6^c^			✓		✓		✓	
	EQ-5D-5L			✓		✓		✓	
	EQ-VAS^d^			✓		✓		✓	
	Cost information					✓		✓	
	Hospital medical records and administrative data							✓	

^a^MHD: monthly headache day.

^b^NRS: numeric rating scale.

^c^HIT-6: Headache Impact Test.

^d^EQ-VAS: EuroQol visual analogue scale.

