### Inclusion Criteria

Inclusion criteria are as follows: (1) adults aged ≥19 years; (2) individuals with a primary diagnosis of primary headache disorders who are first-time outpatients at one of the participating institutions as systematically defined by the *International Classification of Diseases, 10th Revision* (*ICD-10*; G43 [migraine], G44.0 [cluster headaches and other trigeminal autonomic cephalgias], G44.2 [TTH], and G44.8 [other specified headache syndromes]); and (3) individuals who voluntarily agree to participate in the study or whose legal representatives provide both written and verbal informed consent.

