### Measures

#### Baseline Characteristics

The participants’ baseline information will be collected on the first hospital visit. This includes age, gender, monthly household income (in KRW), history of treatment for primary headache disorders and other medical conditions, medication use, occupation and employment status, insurance status, and onset duration (duration from headache onset to first hospital visit).

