#### Clinical Effectiveness

The clinical effectiveness of the treatment will be evaluated using MHDs [36], the NRS [37], the Headache Impact Test (HIT-6) [38,39], the EQ-5D-5L [40], and the EuroQol visual analogue scale (EQ-VAS) [41], with assessments conducted at each study time point: baseline and 6 and 12 weeks. Evidence indicates that increases in MHDs are linked to lower health-related quality of life (HRQOL) and that a reduction in MHDs by ≤4 contributes to improved patient health outcomes [36,42]. Thus, assessing MHDs in this study is crucial for evaluating treatment efficacy. The NRS measures overall pain intensity and discomfort associated with headache, with patients rating their pain on a scale from 0 (no pain) to 10 (worst pain imaginable) [37,43].

The HIT-6 is a widely used validated tool designed to measure the impact of headaches on a patient’s ability to function normally in daily life, comprising 6 items, each with 5 graded response options [38,39]. Each response is assigned a score ranging from 6 to 13 points per item, resulting in total scores that range from 36 to 78, with higher scores indicating greater impact or burden of headaches [44]. The patients’ HRQOL will be evaluated using the Korean version of the EQ-5D-5L [45]. The EQ-5D-5L assesses HRQOL across 5 dimensions: mobility, self-care, usual activities, pain and discomfort, and anxiety and depression [40,46]. The EQ-VAS will be used to measure the patients’ self-perceived health status on a scale from 0 to 100 [41,47]. Higher scores on the EQ-5D-5L and EQ-VAS indicate better HRQOL and overall health, respectively.

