#### Cost-Effectiveness

Cost use for both treatments will be comprehensively assessed, including direct medical costs, direct nonmedical costs, and indirect costs such as productivity losses, derived from CRFs and hospital administrative data. The cost-effectiveness of the treatments will be evaluated using several measures: cost per quality-adjusted life year (QALY) [48,49], the incremental cost-effectiveness ratio (ICER) [50], and the cost-effectiveness acceptability curve (CEAC) [51]. The cost per QALY will be estimated using the area under the curve method [48,52] based on utility scores captured through the EQ-5D-5L and EQ-VAS. The ICER, representing the economic value of collaborative treatment compared with UC, is determined by dividing the incremental cost by the incremental QALYs gained [50,53]. The CEAC illustrates the probability that a treatment is cost-effective across a range of willingness-to-pay thresholds per QALY, with the horizontal axis denoting willingness-to-pay values and the vertical axis representing the corresponding probabilities [51,54].

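### Abstract and Table 1 disagree on whether costs are measured at baseline; if Table 1 governs, incremental cost between self-selected groups cannot be adjusted directly for pre-entry spending or work loss

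*Protocol article*

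**What the plan says.** The Methods paragraph of the abstract states: "Clinical and cost-related outcomes will be assessed at baseline and 6 and 12 weeks".

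Table 1 (Study Design), captioned "Schedule of enrollment and assessments according to the SPIRIT (Standard Protocol Items: Recommendations for Interventional Trials) guidelines", differs. Its row "Cost information" is ticked at 6 and 12 weeks, and its row "Hospital medical records and administrative data" at 12 weeks. The MHD, NRS, HIT-6, EQ-5D-5L and EQ-VAS rows are each ticked at baseline, 6 and 12 weeks.

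The other sections bear on this as follows:

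- **Clinical Effectiveness** ties the three time points, "with assessments conducted at each study time point: baseline and 6 and 12 weeks", to those five measures and does not mention costs.
- **Baseline Characteristics** lists age, gender, household income, treatment history, medication use, occupation and employment, insurance and time since onset. It lists no earlier spending, quantity of resource use or lost work time.
- **Cost-Effectiveness** counts "direct medical costs, direct nonmedical costs, and indirect costs such as productivity losses" and defines the ICER as incremental cost over incremental QALYs.
- **Participants and Treatments** says patients choose their group after a consultation that covers cost implications.
- **Inclusion Criteria** admit "first-time outpatients at one of the participating institutions".

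**The concern.** In a randomised trial, leaving out baseline cost would mainly lose precision. Here the groups form by patient choice, and cost is part of what patients are told before they choose. Earlier spending on headache care and earlier work loss may therefore differ between groups, and both plausibly predict cost over the next 12 weeks. Without a pre-entry measure, a 12-week cost difference mixes the effect of the strategy with what the groups were already spending or losing.

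This is a matter of data collection, not of the covariate list, which an analysis plan could still settle. A variable that was never recorded cannot be added to a model later. Productivity loss is the most exposed component, because hospital records do not hold it and the stated hypothesis takes a societal perspective. At stake is the ICER numerator, and through it the acceptability curve. The clinical comparisons are not touched.

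**Working it through.** **Step 1. What each place says about the timing of cost data.**

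| Place | Baseline | 6 weeks | 12 weeks |
|---|---|---|---|
| Abstract, Methods | yes | yes | yes |
| Table 1, cost row | no | yes | yes |
| Table 1, records and administrative data | no | no | yes |
| Table 1, five clinical outcomes | yes | yes | yes |
| Baseline Characteristics | no cost or work-loss item | – | – |
| Data Collection and Management | CRF holds cost-related details, no time given | – | – |

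The enrollment-only rows, the baseline-only row and the five three-tick rows fix the columns of Table 1. The cost row starts one column after baseline.

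**Step 2. Can the value be recovered later?** Participants are new outpatients at the institution, so its own records should hold little earlier cost. Hospital records do not capture spending elsewhere or lost work. The 12-week extraction is therefore unlikely to fill the gap.

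**Step 3. How large could the bias be?** The documents give no cost figures, so there is no stated value to reproduce, and the inputs marked *assumed* are illustrative.

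- Pre/post cost correlation r: 0.3 to 0.7 (*assumed*)
- Baseline imbalance d: 0.2 to 0.5 SD (*assumed*)
- Analysed per group: 312 × 0.9 / 2 ≈ 140 (from Sample Size Estimation; equal groups *assumed*)

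With similar cost variances before and after entry, the part of the cost difference due to earlier imbalance is about r × d. The SE of the difference is √(2/140) = 0.12 SD.

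| r | d (SD) | Bias r × d (SD) | Bias / SE |
|---|---|---|---|
| 0.3 | 0.2 | 0.06 | 0.5 |
| 0.5 | 0.3 | 0.15 | 1.3 |
| 0.7 | 0.5 | 0.35 | 2.9 |

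**Step 4. Translation to the ICER**, holding the QALY difference fixed.

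- With an *assumed* cost SD of KRW 500,000, the bias is 0.06 × 500,000 = KRW 30,000 up to 0.35 × 500,000 = KRW 175,000 per patient. Dividing by an *assumed* QALY gain of 0.01 gives KRW 3 to 17.5 million per QALY.
- A second set of assumptions takes an earlier imbalance of KRW 50,000 to 100,000, r of 0.3 to 0.7 and a utility gain of 0.02 to 0.10 that builds linearly over 12 weeks. The QALY gain is utility gain × (12/52)/2, or 0.0023 to 0.0115. The cost bias is 0.3 × 50,000 = KRW 15,000 up to 0.7 × 100,000 = KRW 70,000. The ICER shift is 15,000/0.0115 ≈ KRW 1.3 million up to 70,000/0.0023 ≈ KRW 30 million per QALY.

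Both sets show the same thing: over 12 weeks the QALY denominator is small, so a modest cost imbalance is magnified.

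**The case against.** **The abstract may simply be loose.** It is one condensed sentence, and the economic outcomes (QALYs, ICER, acceptability curve) do use baseline EQ-5D-5L. This softens the contradiction but does not remove it: the abstract's next sentence lists EQ-5D-5L and EQ-VAS as clinical outcomes, so they cannot supply the cost-related baseline. If the wording is loose, Table 1 governs and the measurement gap is real.

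**The CRF may contain baseline cost items.** Data Collection and Management says the CRF captures cost-related details and that staff collect baseline and follow-up data. That leaves the point open without settling it. A reader might infer that the study definitely collects no baseline cost. The documents do not support that, because the abstract says the opposite; the consequence is conditional on Table 1.

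**Proxies exist.** A reader might also infer that earlier spending cannot be separated from the treatment effect at all. That goes too far. Income, employment, insurance, medication use, treatment history, baseline MHDs, HIT-6 and EQ-5D-5L plausibly predict later cost and can enter a cost model. None of them measures cost or work loss, so what is lost is direct adjustment.

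**The numbers are assumed.** This stands. The table gives bias before proxy adjustment, its low case is only half an SE, and group sizes set by patient choice may be unequal.

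**The numerator is complete.** Cost collection at 6 and 12 weeks can cover the whole treatment period. This also stands: baseline cost is an adjustment variable, not a missing part of the ICER.

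**Conclusion.** The conflict between the abstract and Table 1 is certain, and no other section resolves it. The consequence is conditional: if Table 1 is followed, incremental cost between self-selected groups cannot be adjusted directly for pre-entry spending or productivity loss, and only partial proxies are available.

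The size and direction of any bias cannot be known from the documents. Under the stated assumptions it lies between about half and about three standard errors of the cost difference before proxy adjustment. Residual bias after proxy adjustment is likely smaller. These figures show that the problem could matter for the ICER; they do not show that the ICER will be wrong by any given amount. The point deserves correction because one of the study's two stated aims rests on this comparison and the change is small.

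**What to change.** Reconcile the two places by ticking cost information at baseline in Table 1, as the abstract already states. Use the existing CRF cost and productivity items with a look-back as long as a follow-up window (six weeks, if each follow-up interview covers the time since the last). Include that baseline cost as a covariate in the cost equation for participants enrolled from then on.

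This may reach only part of the sample. Study Design schedules recruitment to end on December 12, 2025, and Results says only that it was ongoing as of December 2025. For participants already enrolled, or if recruitment has closed:

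- adjust the cost equation for the baseline proxies already collected;
- treat any late recall of pre-entry cost as a sensitivity analysis only, since people already under treatment may recall earlier costs differently according to the group they chose;
- correct the abstract, and state as a limitation that incremental cost is not directly adjusted for prior cost.

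The price is a few minutes per participant at a visit that already takes place, and a small amendment.

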**Results:**

The study protocol was approved by the institutional review boards in July 2025. The study is funded by the Ministry of Health and Welfare, Republic of Korea (grant 202500900001). Participant recruitment commenced in August 2025, aiming to enroll 312 patients across multiple centers. Data collection is currently ongoing and is projected to be completed by December 2027, with results expected to be published in 2028.

**Conclusions:**

This study is designed to generate real-world evidence on whether collaborative treatment yields superior clinical outcomes and greater cost-effectiveness compared to UC for primary headache disorders. The findings are expected to address existing evidence gaps by integrating multidimensional clinical and economic measures, supporting informed decision-making for health policy, and contributing to the advancement of collaborative treatment models for headache management within South Korea’s medical system and beyond.

**International Registered Report Identifier (IRRID):**

DERR1-10.2196/82819

## Introduction

Headache disorders are among the most prevalent neurological conditions worldwide, affecting over 52% of the global population and contributing substantially to disability and health care costs [1,2]. According to the Global Burden of Disease 2019 study, headache disorders rank as the leading cause of years lived with disability worldwide [1,3]. In South Korea, National Health Insurance Service (NHIS) data from 2023 indicate that 580,292 patients were treated for migraine and 543,750 were treated for other headache disorders, such as tension-type headache (TTH), with total health care expenditures exceeding KRW 255.82 billion (US $172.6 million) [4]. Additionally, chronic headaches can lead to reduced productivity, depression, and insomnia [5,6].

Headache disorders are classified into primary and secondary types; primary headache disorders, encompassing migraine and TTH, are estimated to account for approximately 90% of all headache cases [7]. Primary headache disorders are typically managed with pharmacological interventions, whereas the priority for secondary headache disorders lies in identifying and treating the underlying cause [8]. Pharmacological treatments for primary headache disorders—such as nonsteroidal anti-inflammatory drugs and tricyclic antidepressants—often demonstrate limited long-term efficacy and may cause adverse effects [9-11]. Chronic headache in particular is frequently resistant to pharmacotherapy, and overuse of analgesics can exacerbate headache symptoms [9,12].

These substantial impacts underscore the urgent need for structured, multidisciplinary national strategies and alternative approaches for the management and treatment of primary headache disorders [5,13].

Korean medicine (KM) uses a whole person–centered approach, identifying health conditions not merely as localized pathologies but as “patterns” that reflect the systemic active response of the patient. Unlike a disorder diagnosis, which focuses on the pathological process itself, pattern differentiation in KM incorporates systemic findings, innate or acquired constitutional traits, and the balance of yin and yang to capture the individual characteristics of the patient [14,15]. Specifically, electroacupuncture has proven effective in mitigating chronic headache severity, offering a viable option when pharmacological treatments yield limited results [16]. Collaborative treatment aims to integrate these holistic, restorative benefits of KM with the rapid symptom relief provided by Western medicine (WM) [17-20]. There is emerging evidence suggesting that collaborative care can reduce headache frequency and intensity more effectively than monotherapy alone [19,21]. However, robust clinical data comparing the effectiveness and cost-efficiency of collaborative treatment for various health conditions, including primary headache disorders, remain limited [22-24]. Since 1951, South Korea has maintained a dual medical system that legally recognizes both WM and KM [25]. While this structure preserves patient choice and cultural tradition, it can also result in overlapping resources and practice-related disputes [26]. To address these challenges, pilot programs were introduced to support WM-KM collaboration [27]. Despite these initiatives, barriers persist. Treatments from both disciplines provided on the same day for the same condition are typically not jointly reimbursed under the NHIS, resulting in higher out-of-pocket costs for patients [28]. Additionally, limited information exchange and the absence of standardized protocols hinder effective interdisciplinary coordination. To overcome these obstacles, the Korean government launched pilot programs that expanded insurance coverage for collaborative treatment, resulting in improved satisfaction among patients and medical professionals and reduced treatment duration [29,30].

Since its launch in 2016, South Korea’s pilot program for collaborative treatment has progressed through 4 stages and is now preparing for its fifth phase [28,30]. The program has gradually evolved from parallel practice to protocol-based models for specific conditions, along with a unified reimbursement system and strengthened institutional support for collaborative treatment [24,30,31]. Notable advancements include the introduction of interinstitutional electronic medical record sharing systems and joint training programs for WM and KM practitioners. Nonetheless, persistent challenges—such as fragmented delivery systems, insufficient clinical experience with interdisciplinary practice, and the lack of unified clinical guidelines—continue to limit the wider adoption of collaborative care models. To address these gaps and validate the feasibility of a structured collaborative model before a large-scale trial, preliminary data are required. Before designing this multicenter trial, we conducted an internal pilot study (KCT0010198) involving 59 patients with primary headache disorders to assess feasibility and preliminary efficacy.

The primary objective of this multicenter study is to investigate whether collaborative treatment provides greater clinical effectiveness and cost-efficiency for patients with primary headache disorders compared to usual care (UC) alone. We hypothesize that patients receiving collaborative treatment will exhibit significantly greater improvements in headache intensity (numeric rating scale; NRS) and frequency (monthly headache days; MHDs) compared to those receiving UC and that collaborative treatment will prove to be a cost-effective strategy from a societal perspective. To achieve this, we will conduct a prospective, multicenter observational study using validated patient-centered instruments focusing on headache-related disability, quality of life, and self-rated health status alongside an economic evaluation based on health care costs and utility measures.

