### Sample Size Estimation

To determine the appropriate sample size, we referenced data from our preceding pilot study, which was a multicenter prospective observational study conducted across 5 medical institutions during the fourth phase of the national collaborative treatment pilot project (December 2023-December 2024). This pilot study aimed to assess the feasibility and preliminary clinical effectiveness of collaborative treatment versus UC in patients with migraine (*ICD-10* code G43) and other headache syndromes (*ICD-10* code G44; Clinical Research Information Service registration KCT0010198). On the basis of the analysis of 59 participants from this pilot study, the NRS values were derived (group 1: mean 1.85, SD 1.66; group 2: mean 2.48, SD 2.13). Using the G*Power program with a 2-sided significance level of .05 and power of 80% (α=.05) and adjusting for a 10% discontinuation rate, the total required sample size for the study was determined to be 312 participants.

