### Statistical Analyses

Baseline data will be summarized using descriptive statistics such as percentages, frequencies, and means and SDs for both the UC and collaborative treatment groups. The UC group refers to participants receiving treatment exclusively with either KM or WM, whereas the collaborative treatment group includes those receiving both KM and WM. Data normality will be evaluated using the Shapiro-Wilk test and *Q*-*Q* plots. Between-group differences will be assessed using chi-square tests (Fisher exact test) for categorical data and the 2-tailed Student *t* test or ANOVA for continuous data. When normality or equal variance assumptions are violated, the Mann-Whitney *U* test and Kruskal-Wallis test will be performed.

Per-protocol and intention-to-treat (ITT) analyses will be conducted to assess clinical effectiveness and cost-effectiveness. To establish the ITT dataset, the proportion and mechanism of missing data will be evaluated using the Little test. If the data are identified as missing completely at random or missing at random, as defined by Rubin [55], multiple imputation will be performed [55,56]. Mean changes in clinical outcomes over time will be compared between groups as part of the effectiveness analysis. Furthermore, a generalized linear mixed model will be used to assess between-group effects at each time point. To rigorously control for heterogeneity and potential confounders, the model will adjust for fixed effects, including age, sex, headache history (onset duration), specific diagnosis, and comorbidities. While specific treatment modalities vary, reflecting real-world practice, the analysis adheres to the ITT principle to evaluate the effectiveness of the collaborative treatment strategy compared to UC rather than the efficacy of individual modalities. Subgroup analyses will be performed according to headache type (migraine, TTH, or other) and headache severity (episodic or chronic).

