Utility values from the EQ-5D-5L and EQ-VAS will be used to estimate QALYs using the area under the curve method [48]. Deterministic analyses for the ICER will be performed using both ITT and per-protocol data from a limited societal perspective and a societal perspective. A probabilistic sensitivity analysis will also be carried out using parameter distributions and estimates. To account for sampling uncertainty in the ICER point estimates, 95% CIs will be calculated using the bootstrapping method or a seemingly unrelated regression model. All statistical analyses will be conducted using Stata/MP (version 14.0; StataCorp) and SAS (version 9.4; SAS Institute), with the significance level set at a *P* value of <.05.

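### The hypothesis predicts significance on both pain intensity (NRS) and monthly headache days, but the sample size covers NRS alone and no deciding outcome, time point or success rule is named

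*Protocol article*

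**What the plan says.** - **Hypothesis (Introduction, last paragraph).** Patients on collaborative treatment are expected to show "significantly greater improvements in headache intensity (numeric rating scale; NRS) and frequency (monthly headache days; MHDs) compared to those receiving UC". Cost-effectiveness is added as a further expectation. No week and no analysis set is attached. The Discussion (Anticipated Findings) again names both headache frequency and intensity.
- **Sample size (Methods, Sample Size Estimation).** From 59 pilot participants, "the NRS values were derived (group 1: mean 1.85, SD 1.66; group 2: mean 2.48, SD 2.13"). The settings are "Using the G*Power program with a 2-sided significance level of .05 and power of 80% (α=.05"), then "adjusting for a 10% discontinuation rate", and "the total required sample size for the study was determined to be 312 participants". The section does not say whether the NRS values are scores or changes, or which week they come from. MHDs do not enter.
- **Outcomes (Methods, Clinical Effectiveness).** Five clinical outcomes are measured at baseline, 6 and 12 weeks. None is called primary, and MHDs are described as crucial to judging efficacy.
- **Analysis (Methods, Statistical Analyses).** A mixed model is used to "assess between-group effects at each time point". Intention-to-treat (ITT) and per-protocol analyses are both run, with ITT named as the guiding principle. All analyses are done "with the significance level set at a" P value below .05.

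**The concern.** The study makes a two-outcome prediction and justifies its size with a one-outcome calculation. A reader who joins the two will take the 80% power as applying to the hypothesis as worded, and nothing in the article supports that.

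The success rule is also open. With NRS and MHDs each tested at two weeks, there are four results on which a positive headline could rest. The findings are meant to inform practice guidelines and reimbursement (Discussion, Dissemination and Future Directions), so it matters whether a claim rests on a test fixed beforehand or on whichever result fell below .05.

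**Working it through.** **Inputs from the article.** NRS 1.85 (SD 1.66) and 2.48 (SD 2.13); two-sided alpha .05; power 80%; discontinuation 10%; N = 312.

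**Assumed, because the article gives no figure.** 1:1 groups; unadjusted two-sample t test; MHD standardised effect d of 0.20, 0.33 or 0.40; correlation r between the NRS and MHD test statistics from 0 to 0.7.

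**Step 1: the plan's own figure.**
- Difference = 2.48 − 1.85 = 0.63. SD = √[(1.66² + 2.13²)/2] = 1.91. d = 0.63/1.91 = 0.330.
- Normal approximation: n per arm = 2(1.960 + 0.842)²/0.330² = 144.2, so 145. The t test gives 146, or 292 in total.
- Dropout: 146/0.9 gives 163 per arm, or 326; multiplying 292 by 1.1 instead gives 322.
- The stated 312 is slightly lower. An unequal pilot split would explain it: 34/25, which the article does not state, gives a pooled SD of 1.872, 140 per arm, and 2 × 156 = 312 after dropout. I do not call 312 an error. It is an NRS-only number with no allowance for a second outcome.

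**Step 2: NRS power at the stated size.**
- Evaluable: 312 × 0.9 = 280.8, about 281, or 140.5 per arm.
- Noncentrality = 0.330 × √(140.5/2) = 2.765. The t test power is 0.787.

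**Step 3: if both NRS and MHDs must be significant at one week.** Joint power is P(both statistics exceed the critical value). At r = 0 it is the product of the two powers; for r > 0 it is a bivariate normal probability.

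| MHD effect (assumed) | MHD power | Joint, r = 0 | Joint, r = 0.7 |
|---|---|---|---|
| 0.20 | 0.386 | 0.787 × 0.386 = 0.304 | 0.375 |
| 0.33 | 0.787 | 0.787 × 0.787 = 0.619 | 0.696 |
| 0.40 | 0.916 | 0.787 × 0.916 = 0.721 | 0.765 |

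If both outcomes are instead given exactly 80% power, the range is 0.64 (0.80²) to 0.71. Joint power can never exceed the NRS power, whatever the MHD effect. For 80% joint power at equal effects, 174 (r = 0.7) to 190 (r = 0) evaluable per arm are needed. After 10% dropout that is 2 × 194 = 388 to 2 × 212 = 424 enrolled.

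The error rate for the joint claim at one fixed week stays at or below .05, because both tests must pass. If the week is left open and NRS truly improves while MHDs do not, the MHD test has two chances. The error is then about 8% to 9% for correlations of 0.7 to 0.5 between weeks.

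**Step 4: if either outcome is enough.**
- One week, two tests: 1 − 0.95² = 9.8% if independent, 8.3% at r = 0.7.
- Two weeks, four tests: 1 − 0.95⁴ = 18.5% if independent. Simulation with correlation 0.3 to 0.5 between outcomes and 0.5 to 0.7 between weeks gives 15% to 17%.

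**The case against.** Several points on the other side stand.

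- **Both faults at once.** A reader might infer that the plan both fails to control error and fails to power its claim. For the NRS/MHD pair at one week these are alternatives. If both must succeed, testing each at .05 is valid and only power is short. If either suffices, error is inflated, but NRS was sized.
- **What the hypothesis claims.** It might be read as promising significance at two weeks and in two populations. It names neither; the two weeks come from the analysis section.
- **ITT and per-protocol.** Counting them as separate chances of success is not supported. The Statistical Analyses section names ITT as the governing principle, so per-protocol is not counted above.
- **All five outcomes.** One could count five outcomes at two weeks, with an error rate near 32% at an assumed correlation of 0.4. The hypothesis names only two clinical outcomes, so that figure does not describe it.
- **An unseen analysis plan.** A multiplicity procedure may be set out there, and its absence from a condensed article is no finding. That does not answer the mismatch: the hypothesis and the sample size basis are both printed and do not agree, and an analysis plan cannot supply power that the calculation did not provide for.
- **Assumed effects.** Every joint power figure depends on an MHD effect that the article does not give. Only the ceiling, the NRS power itself, is free of that assumption.

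**Conclusion.** The point holds as a mismatch between claim and sample size, with the deciding test left open. Which consequence follows depends on a success rule that the article does not state:

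- **Both required:** the error rate is held at a fixed week. Joint power is at most about 0.79, and 0.62 to 0.70 if MHDs share the NRS effect. It is 0.30 to 0.37 at an MHD effect of 0.20 and 0.72 to 0.77 at 0.40.
- **Either enough:** the error rate is about 8% to 10% at one week and about 16% over both, up to 18.5% if the tests are independent.

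The power figures assume 281 evaluable participants in equal groups. Patients choose their treatment, so the groups may be uneven, which would generally lower power further. The documents do not support saying that the joint claim has a known low power; they support saying that its power is not shown and is not the stated 80%. This should be corrected, but it does not invalidate the NRS-based calculation as a calculation for NRS.

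**What to change.** 1. Name one confirmatory test: the adjusted between-group difference in NRS at one time point, in the ITT set, at two-sided .05. Use week 12, or whichever time point and scale the pilot NRS values represent, and state in the Sample Size Estimation section what those values are. Until that is stated, it cannot be said that 312 gives 80% power for NRS at week 12.
2. Test MHDs at the same time point only if NRS is significant. This fixed sequence needs no split of alpha.
3. Report the other time point, HIT-6, EQ-5D-5L, EQ-VAS, subgroups and the per-protocol analysis as supportive estimates with 95% CIs.
4. Reword the hypothesis so that 80% power is claimed for NRS only.

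If NRS and MHDs are kept as co-primary outcomes, state the joint power under an explicit MHD effect and correlation. At equal effects, keeping 80% would need about 388 to 424 enrolled rather than 312.

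The cost is a wording amendment while data collection is still running (projected to December 2027), with a check that the registration record agrees. The downside is that MHDs become a second-step test and the power claim is narrower. The sequence controls error but does not raise the chance of succeeding on both outcomes, which stays at the joint power shown above.
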